## Background

With contemporary therapies, over 80% of children diagnosed with cancer will become long-term survivors [1, 2]. The childhood cancer survivor (CCS) population in the United States exceeds 390,000 [3]. CCS are at significant risk of serious morbidity and premature mortality as a result of their cancer therapy [4, 5]. Cardiac toxicity, mainly caused by anthracycline chemotherapy agents (e.g. doxorubicin, daunomycin) which are administered to more than 50% of children with cancer [6], is a major cause of this morbidity. Although observed frequencies vary between studies, up to 60% of patients treated with an anthracycline will develop echocardiographic abnormalities [7]. These abnormalities increase over time in incidence and severity in a significant proportion of patients [8–10]. The risk of congestive heart failure (CHF) in children exposed to a cumulative anthracycline dose greater than 300 mg/m^2^ approaches 10% by 20 years after their cancer therapy [11], but even children exposed to lower doses of anthracyclines are at significantly increased risk for CHF [7, 12]. Compared to their siblings, CCSs have a 15-fold increased risk of developing CHF [13]. Cardiac disease is the third leading cause of premature death in CCS (after cancer recurrence and second malignancies), with a 7-fold increased risk of premature cardiac death as compared to the general population. The relative risk of cardiac death remains elevated even in CCS who have survived for more than 25 years after their primary cancer [14].

Clinicians rely on established clinical risk factors (e.g. cumulative anthracycline dose, radiation therapy to a field that involves the heart, younger age at treatment, female gender, longer follow-up, and CHF during therapy [7–9, 15–19]) in order to identify which children treated for cancer are at risk for late-onset cardiac dysfunction. The Children’s Oncology Group guidelines for surveillance for late effects in CCS recommend a surveillance echocardiogram or MUltiGated Acquisition scan (MUGA) every 1, 2, or 5 years depending on three risk factors: (1) age at treatment; (2) cumulative anthracycline dose; and (3) receipt of chest radiation [20–22]. However, these factors are imperfect predictors, and do not take into account individual biological variations in metabolism of chemotherapy and response to cardiac injury. Consequently, their discriminative power for individual patient decision making is poor [23].

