#### Aim 1 (acute cohort)

To determine and validate which of the currently available dynamic protein biomarkers detectable in serum during the acute phase of anthracycline administration can predict early cardiac remodeling.

A panel of biomarkers that have been shown to indicate cardiac stress or injury, including N-terminal pro b-type natriuretic peptide (NTproBNP), high sensitivity troponin (hsTnT), myeloperoxidase (MPO), and insulin-like growth factor binding protein 7 (IGF-BP7) will be evaluated. The discovery cohort will be derived from the children enrolled in the Acute Cohort at The Hospital for Sick Children. The validation cohort will be derived from similarly recruited patients in the Acute Cohort from London, Ottawa and Hamilton. Patients will have serum collected at the time points specified in Fig. 1. The serial serum samples will be assayed for levels of the target markers at each of the collection time points. Both the individual marker levels and the patterns of change over time will be evaluated against the primary outcome (evidence of remodeling, decreased EF or CHF at 1 year). The candidate biomarkers will be evaluated using quality controlled assays on the most appropriate platforms (e.g. for NTproBNP, hsTnT and IGF-BP7, the Roche Elecsys platform available in the Biomarker Core laboratory will be used, and for MPO, standard human serum ELISA kits such as that provided by Eagle Bioscience, NH will be used). These will be performed in replicate with appropriate controls. The best candidates from the discovery cohort will then be applied to the validation cohort to determine the reproducibility and cross population validity of the marker performance.

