### Developing a risk prediction model

To achieve the primary objective of the Acute Cohort study (identifying patients at increased risk for therapy-induced cardiac disease prior to starting or during therapy), evolution of echocardiographic parameters over the treatment duration will be modeled in linear and non-linear regression models adjusted for repeated measures through a compound symmetry covariance structure. The resulting general estimating equations (GEE) will provide an estimate of the effect of anthracyclines over time for the entire cohort and the parameter estimate (slope of change over time) for each individual patient will be used as a potential predictor of therapy-induced cardiac damage. Twelve months after their final cycle of anthracycline chemotherapy, patients will be classified as having cardiac disease or not based on evidence of remodeling or decreased EF or CHF. Potential factors associated with acute cardiac change or cardiac damage at 12 months after treatment will be sought from patient demographics (e.g. age at treatment, gender), treatment (e.g. cumulative anthracycline dose, radiation exposure), genomics, serial biomarkers and echocardiographic measurements at baseline and during follow-up. Because of the very large number of potentially associated factors (and the multiple variations in format/time points for many factors), we will have to reduce the number of candidate factors using a pre-specified algorithm. As exploratory analyses, univariate regression models using therapy-induced cardiac changes or cardiac disease at 1 year (present vs. absent) as the dependent variable, and all other collected variables as potential independent variables will be created. This will allow exploration of variables potentially associated with therapy-induced cardiac damage including assessment of collinearity, ill condition (variables with no events in one of the study groups) or amount of missing data. All variables with univariable *p*-value <0.30, excluding collinear variables, ill conditioned variables or variables with an unacceptable amount of missing data will be included in a bootstrap bagging algorithm. A total of 5000 random sub-samples will be created and for each of those, a mixed stepwise regression model will be used to obtain multivariable predictors for therapy-induced cardiac damage. The proportion of sub-samples in which a given variable is selected is called reliability. Variables with high reliability (>50%) will then be included in a multivariable regression model with backward selection of variables to obtain a final model. This algorithm significantly improves the accuracy of variable selection, reduces the probability of sampling bias and corrects for multiple comparisons better than a post-hoc analysis would. At the end of this algorithm we will be left with a limited number of associated factors, all with high reliability. Based on the reliability estimates, we will be able to determine whether the risk of therapy-induced cardiac changes or cardiac damage at 1 year after anthracycline exposure is driven by baseline measurements (including clinical, genomic, echocardiographic or biomarkers), by reaching specific milestones during anthracycline treatment, by change over time in cardiac dimension/function and biomarkers during anthracycline treatment, or by a combination of all three.

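### The risk model puts the established clinical factors through the same data-driven selection as the new markers, so it neither ensures that they stay in nor establishes what the markers add

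*Protocol article*

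**What the plan says.** The Background lists the factors that clinicians already use, among them "cumulative anthracycline dose, radiation therapy to a field that involves the heart, younger age at treatment, female gender". It adds that age at treatment, cumulative dose and chest radiation set the surveillance interval, and that these factors discriminate poorly for the individual patient. The fourth study aim is a model that joins genomic, biomarker and imaging data with clinical data, and the Discussion expects genetic predictors to be combined with clinical risk factors.

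Developing a risk prediction model then fixes the method for the Acute Cohort. Predictors of the 12-month outcome "will be sought from patient demographics (e.g. age at treatment, gender), treatment (e.g. cumulative anthracycline dose, radiation exposure), genomics, serial biomarkers and echocardiographic measurements". The section gives the reason for selecting among them: "Because of the very large number of potentially associated factors". Selection has three steps:

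1. Univariable screening at a p-"value <0.30, excluding collinear variables, ill conditioned variables" and variables with too much missing data.
2. Resampling: "A total of 5000 random sub-samples will be created and for each of those, a mixed stepwise regression model will be used".
3. Final model: "Variables with high reliability (>50%) will then be included in a multivariable regression model with backward selection of variables to obtain a final model".

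No variable is exempt from any step, and no clinical-only comparison model is described. The section intends to read from the reliability estimates whether risk is driven by baseline values, by milestones during treatment, or by change over time.

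**The concern.** The study exists because the current clinical factors predict imperfectly. The useful question is therefore what genes, biomarkers and imaging add to them, and that needs a fixed clinical reference. Under the stated algorithm the clinical part of the model is whatever survives selection, and it could be empty.

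Three things follow. A true factor of moderate effect can drop out because the cohort is small for selection, not because the factor is irrelevant, and prediction suffers. Collinear variables are removed with no rule on which of a pair goes, so a marker that tracks cumulative dose could displace dose itself. And selection frequency among correlated candidates does not measure added value: a marker chosen in most sub-samples may be standing in for a clinical factor that was left out.

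**Working it through.** **Inputs from the article.** Acute Cohort target 270, actual 307; one binary outcome per child at 12 months; screen p<0.30; 5000 sub-samples; reliability above 50%; then backward selection. Prior chest radiation is an exclusion criterion (Table 1), so radiation varies only through the current treatment.

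**Inputs assumed, because the article gives none.** Event rate 10 to 40%; stepwise entry and stay thresholds 0.05 or 0.15; final removal at 0.05; dose and age standardised; half the children female; 15% with heart-field radiation. Assumed true odds ratios:

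| Setting | Dose per SD | Age per SD | Sex | Radiation |
|---|---|---|---|---|
| Weak | 1.3 | 1.25 | 1.3 | 1.5 |
| Moderate | 1.5 | 1.4 | 1.5 | 2.0 |
| Strong | 2.0 | 1.6 | 2.0 | 3.0 |
| Very strong | 2.5 | 2.0 | 2.5 | 4.0 |

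The article states no power or sample-size calculation, so there is no figure of its own to reproduce.

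**Hand check.** The chance of keeping a factor at two-sided 0.05 is about Φ(z − 1.96), with z = ln(OR) × √(n p (1−p) Var(x)). Take moderate effects, n = 307 and 20% events: n p (1−p) = 307 × 0.2 × 0.8 = 49.12, with square root 7.009.

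- Dose: z = 0.405 × 7.009 × 1 = 2.84, chance 0.81.
- Age: z = 0.336 × 7.009 × 1 = 2.36, chance 0.66.
- Sex, variance 0.25: z = 0.405 × 7.009 × 0.5 = 1.42, chance 0.30.
- Radiation, variance 0.15 × 0.85 = 0.1275: z = 0.693 × 7.009 × 0.357 = 1.73, chance 0.41.
- All four, if independent: 0.81 × 0.66 × 0.30 × 0.41 ≈ 0.06.

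Across n = 240 to 307, 10 to 40% events and thresholds of 0.05 or 0.15, the chance of keeping all four is 0 to 9% (weak), 0.5 to 42% (moderate) and 9 to 91% (strong).

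**Simulation of the stated algorithm.** n = 307, 60 bootstrap samples in place of 5000, 120 to 200 replicates per setting, one to three real new markers (OR 1.5 per SD, one correlated 0.5 with dose), and 2 to 100 noise candidates.

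| Setting | All four kept | At least one lost |
|---|---|---|
| Weak, 20–35% events | 0–1% | 99–100% |
| Moderate, 10–35% events | 2–12% | 88–98% |
| Strong, 30 noise candidates | 29–45% | 55–71% |
| Strong, 2 noise candidates | 48–62% | 38–52% |
| Very strong, 30% events | 76% | 24% |

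A second simulation used six noise variables, slightly larger dose and age effects (OR 1.5 or 1.8 and 1.5), and backward selection in 30 resamples. It lost at least one factor in about 98% of trials at 15% events and in 86 to 91% at 30%.

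By factor, under moderate effects with 20 to 35% events and 30 noise candidates: dose kept in 61 to 75%, age 48 to 72%, sex 22 to 32%, radiation 41 to 55%. Under strong effects: 92 to 100%, 78 to 93%, 55 to 64% and 72 to 84%. With moderate effects and 10% events (about 31 children), dose is kept in 48%.

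**Effect on prediction (out-of-sample AUC).** The forced-in model is the four clinical factors plus the new variables that the stated algorithm picked; selection was not rerun around the forced factors.

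| Setting | Clinical only | Stated algorithm | Forced in | Forced − stated |
|---|---|---|---|---|
| Moderate, 30% events, 30 noise | 0.674 | 0.695 | 0.709 | 0.014 |
| Strong, same | 0.745 | 0.755 | 0.764 | 0.009 |
| Very strong, same | 0.795 | 0.802 | 0.806 | 0.004 |
| Moderate, 10% events, 30 noise | 0.673 | 0.658 | 0.683 | 0.025 |
| Moderate, 30% events, 100 noise | 0.673 | 0.665 | 0.681 | 0.016 |

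With only 2 noise candidates the gain is 0.004 to 0.016. The stated algorithm falls clearly below the clinical-only model only with few events or very many candidates.

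**The case against.** The strongest reply has four parts.

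First, an article condenses the full protocol, and nothing in it forbids a clinical-only comparison. A reader might infer that the study cannot show what the new data add. The text does not support that: such a model could still be fitted, and the Genomics Core already puts non-genetic predictors in its own regression. What stands is narrower. The selection algorithm is written out step by step as pre-specified, and it is this algorithm that treats the clinical factors as ordinary candidates.

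Second, the loss rates depend on chosen effect sizes and on a joint measure. Even 80% retention of each factor would lose at least one in 1 − 0.8⁴ = 59% of trials if they were independent, and sex, the least often kept, drives much of the result. A reader might infer that real factors will usually be dropped whatever the truth. That fails under very strong effects, often under strong effects with few candidates, and for dose alone in most settings.

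Third, the Background ties these factors to late-onset dysfunction, whereas the model's outcome is a 12-month composite that includes wall-thickness change. The article does not say that they are established for that outcome, and radiation may be sparse. This stands as a caution. It does not remove the need for a clinical reference, since these are the factors that clinicians now use.

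Fourth, a reader might extend the point to Biomarker Core Aim 1, where "Both the individual marker levels and the patterns of change over time will be evaluated against the primary outcome", and infer unadjusted testing. That sentence names no model and is silent on covariates. Silence in a condensed article is not a decision to leave them out, so the point does not extend there.

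**Conclusion.** The concern holds for the integrated risk model. As described, its algorithm does not ensure that age at treatment, sex, cumulative dose and heart-field radiation stay in, and added value over them is not established by the final model or by the reliability estimates.

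How often a true factor is lost depends on effect sizes, event rate, candidate count and stepwise thresholds, none of which the article gives. It is most trials under assumed weak to moderate effects, somewhat more than half under strong effects with many candidates, and a minority under very strong effects. The cost to prediction is modest. The stronger reason to change is that the model lacks a fixed clinical reference for the question that the study sets itself. This is a cheap improvement to a stated method, not a flaw that invalidates the study.

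**What to change.** In Developing a risk prediction model, state that age at treatment, sex and cumulative anthracycline dose enter every resample and the final model, exempt from the p<0.30 screen, the collinearity exclusion, the reliability rule and backward elimination. Treat heart-field radiation the same way if enough children are exposed for it not to be ill-conditioned, and state that condition in advance. Where a new marker is collinear with dose, keep dose. Apply selection only to the genomic, biomarker and imaging candidates. Report the clinical-only model beside the full model, each with an optimism-corrected C-statistic.

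The cost is wording, because demographics and cancer therapy are already collected (Table 2). About four degrees of freedom are always spent, against about 61 events at an assumed 20% rate (307 × 0.2), so slightly fewer novel factors may be selected.

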### Acute cohort

A prospective cohort of patients newly diagnosed with cancer who received anthracycline chemotherapy has been recruited from clinics at the four pediatric participating centres (recruitment target *n* = 270; recruitment actual *n* = 307). We will assess whether genetic predictors of anthracycline susceptibility, biomarkers of early cardiac damage, and imaging parameters of acute cardiac dysfunction predict which patients will demonstrate evidence of persistent or progressive cardiac damage at the 12 months follow-up from their last cycle of anthracycline chemotherapy (See Fig. 1 for timeline of sample and data acquisition in Acute Cohort). Eligibility criteria for both cohorts are provided in Table 1.

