### Study outcomes

Based on paediatric and adult data that show that early cardiac remodelling precedes global dysfunction, the study will use remodeling parameters (left ventricular posterior wall thickness (LVPWT) Z-score and LV thickness to dimension ratio (TDR)) as markers of early cardiac injury that can identify patients who are at risk for progressive cardiac dysfunction later in life. Thus, the primary outcome measurement in each of the genomics, biomarker and imaging cores is the presence of one or more of the following at 12 months after anthracycline in the Acute Cohort, or at any study time point in the Survivor Cohort:Cardiac remodelling defined as an LVPWT or TDR z-score < −2.0 (or a reduction in LVPWT or TDR z-score by ≥1 standard deviation compared to baseline in the Acute group); orReduced LV EF (<55%) or a drop in LV EF of ≥10% over serial echocardiograms; orSymptomatic heart failure graded using New York Heart Association (NYHA) classification (or Ross heart failure class 2 in infants <2 years old).

This study is being conducted by three collaborative cores:

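### Candidate predictors of the 12-month outcome have no cut-off before the 12-month visit and share the baseline echo with the outcome, so apparent prediction is inflated even without cardiac injury

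*Protocol article*

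**What the plan says.** Under Study outcomes, an Acute Cohort child is a case if any of several criteria is met 12 months after anthracycline. Some are absolute: an LVPWT or TDR z-score below -2.0, EF below 55%, or symptomatic heart failure. Others are changes: "a reduction in LVPWT or TDR z-score by ≥1 standard deviation compared to baseline in the Acute group", or "a drop in LV EF of ≥10% over serial echocardiograms".

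Under Developing a risk prediction model, "patients will be classified as having cardiac disease or not based on evidence of remodeling or decreased EF or CHF". Candidate predictors come from demographics, treatment, genomics and "serial biomarkers and echocardiographic measurements at baseline and during follow-up". Each child's slope of the echo parameters, modelled over the treatment period, is also a candidate. The univariable screen is then opened to everything recorded: "and all other collected variables as potential independent variables will be created". A variable leaves the list if its univariable p-value is 0.30 or more, or if it is collinear, ill-conditioned or has too much missing data. The rest go through 5000 sub-samples with stepwise selection, and those chosen in more than 50% of them enter the final model.

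The stated purpose is "identifying patients at increased risk for therapy-induced cardiac disease prior to starting or during therapy". The section ends by saying that the selection frequencies will show whether risk comes from baseline measurements, milestones during treatment, change during treatment, or a combination.

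For the Biomarker Core, Aim 1 (acute cohort): "Both the individual marker levels and the patterns of change over time will be evaluated against the primary outcome". Table 2 schedules optional biomarker samples up to the 12-month visit.

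**The concern.** The outcome is built from LVPWT, TDR and EF at month 12 and, for its change components, at baseline. The same measurements can enter as predictors, for two reasons.

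- **No time cut-off.** Nothing in the exclusions keeps values from the 12-month visit out. An echo value from that visit is part of the outcome, and a biomarker from that visit is concurrent with it. Neither can predict it.
- **Shared baseline.** A baseline reading that is high by chance makes a later fall more likely. It also makes the baseline predictor high and tilts any slope that starts at baseline downwards. Predictor and outcome are then associated through measurement error alone.

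The existing safeguards do not touch either problem. The collinearity rule compares predictors with each other, not with the outcome. Resampling does not help, because the shared error is present in every sub-sample; a high selection frequency would only show that the artefact is stable.

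At stake is the closing attribution of risk to baseline status or to change during treatment, since baseline echo values and slopes are exactly what the artefact favours. The Discussion expects the resulting algorithm to inform clinical decisions.

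**Working it through.** The article gives no AUC, event rate or sample-size calculation for the model, so there is no figure of the plan's own to reproduce.

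**Step 1: why the association arises without injury.** Let a child's true level T be constant and each echo be T plus independent error with SD s. Let the total SD be S, and let repeatability be ICC = 1 - s²/S². The fall from baseline to month 12 is D = e0 - e12, with variance 2s².

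- Baseline value against D: correlation = s² / (S · √2 · s) = √((1 - ICC)/2). For ICC 0.5, 0.7, 0.8 and 0.9 this is 0.50, 0.39, 0.32 and 0.22. The 12-month value has the same correlation with opposite sign.
- Least-squares slope over five equally spaced echoes starting at baseline: weights (-2, -1, 0, 1, 2)/10, variance 0.1s², covariance with D = -0.2s². Correlation = -0.2/√(0.1 × 2) = -0.45, whatever the ICC.
- Slope without the baseline echo: covariance with D = 0. The artefact disappears.

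**Step 2: size on the composite outcome.** Null simulation with constant true levels.

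- From the article: outcome criteria other than heart failure; entry rule EF above 55%; echoes at baseline, before each dose and at month 12; Acute Cohort "recruitment actual *n* = 307".
- Assumed: z-scores with total SD 1; ICC 0.5 to 0.9; LVPWT-TDR correlation 0.6; EF mean 63, between-child SD 3.5, within-child SD 4.5 down to 2.0; five echoes up to the last pre-dose visit plus month 12; least-squares slopes.
- Method: logistic models fitted on 60,000 simulated children (before the EF entry filter), AUC taken on a separate 60,000.

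The EF drop was read in two ways, because the article does not say which echoes are compared.

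| Candidates (LVPWT, TDR, EF) | EF drop: baseline to month 12 | EF drop: between any serial echoes |
|---|---|---|
| Baseline only | 0.54-0.72 | 0.51-0.71 |
| Treatment slopes only | 0.57-0.65 | 0.57-0.66 |
| Baseline, slopes, last pre-dose values | 0.67-0.77 | 0.64-0.76 |
| The same plus 12-month values | 0.88-0.90 | 0.78-0.88 |

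The share of children classed as cases with no injury was 7.5% to 34% on the first reading and 7.7% to 60% on the second.

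**Step 3: the screen at the actual sample size.** This used 400 null data sets of 307 children at each of ICC 0.5, 0.7 and 0.9, with the first reading of the EF drop. A variable unrelated to the outcome would pass p < 0.30 in about 30% of data sets and p < 0.05 in about 5%.

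| Variable | p < 0.30 | p < 0.05 |
|---|---|---|
| Baseline LVPWT z | 73-99% | 38-94% |
| LVPWT slope during treatment | 59-100% | 22-95% |
| 12-month LVPWT z | 100% | 99-100% |

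**Step 4: isolating the cause.** For LVPWT alone, with between-child SD 0.8 and measurement SD 0.6 (both assumed) and the z below -2 criterion included, the null AUC is about 0.65 for baseline, 0.71 for the treatment slope and 0.76 for the 12-month value. Dropping the baseline echo from the slope returns it to 0.50, as Step 1 predicts.

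**The case against.** Much can be said for the plan.

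- **The 12-month echo is not named as a predictor.** Slopes are modelled over treatment, and the closing sentence speaks of baseline and of events during treatment. This stands: 12-month values enter only through open wording. A reader might infer that strong false prediction is certain. Null AUCs of 0.93 (LVPWT) and 0.96 (EF) do arise for a slope that runs to month 12, but the article describes no such slope.
- **The absolute thresholds work against the change criteria.** This also stands. For EF alone, under one assumed pair of SDs (4 and 4 points), adding EF below 55% and the entry rule moves the null AUC for baseline from 0.79 to about 0.46. Single-criterion figures therefore overstate the effect on the composite.
- **Predicting a later echo from earlier ones is a stated aim.** Correct, so earlier LVPWT, TDR and EF should not be barred. Part of the null AUC also comes from children whose values are persistently low-normal. That association is real and reproducible, but it is not therapy-induced injury.
- **Slopes are available during therapy.** The last scheduled on-treatment echo precedes the last dose, so it would be wrong to say that slopes cannot serve an on-therapy model.
- **Serum markers share no echo error.** True, and Biomarker Aim 1 is worded around the acute phase. Only the 12-month sample is a problem there.
- **The article is condensed.** It nevertheless states both the candidate scope and the list of exclusions. The rule as written has the gap, so this is more than missing detail.

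A reader might also infer that genomic, strain and biomarker predictors will be crowded out. No calculation here includes such predictors or runs the resampling, so that is not shown.

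**Conclusion.** The point holds in a bounded form. Followed as written, the rule admits outcome-visit values and leaves the shared baseline echo uncorrected, so the composite outcome appears predictable in children with no injury. The inflation is strong if 12-month values enter (null AUC about 0.78 to 0.90) and moderate if candidates stop at the last pre-dose echo (about 0.64 to 0.77; treatment slopes alone about 0.57 to 0.65). The planned attribution of risk to baseline or to change during treatment cannot be trusted without correction.

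The direction follows from the definitions. The sizes rest on the assumed repeatability, SDs and number of echoes, and on the reading of the EF drop. The documents do not support a claim that the model will necessarily show strong false prediction. The data collection is unaffected.

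**What to change.** Amend Developing a risk prediction model as follows.

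1. State a landmark for each model. The pre-therapy model uses baseline data only; the on-therapy model uses data up to the last pre-dose visit.
2. Bar all 12-month echo and biomarker values as predictors, including in Biomarker Core Aim 1.
3. Keep earlier LVPWT, TDR and EF as candidates, but compute their slopes without the baseline echo.
4. For the change-defined components, model the 12-month value with the baseline value forced in.
5. State which echoes count for the EF drop. If any serial pair counts, on-treatment EF values are themselves part of the outcome, and step 3 alone does not remove the overlap for EF.
6. Report model performance with and without the outcome-defining parameters.

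No new data are needed. The costs are slightly less precise slopes, because one echo is dropped, and a less favourable apparent performance.
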